## Abstract

**Background:**

Incomplete vascularization of the retina in preterm infants carries a risk of retinopathy of prematurity (ROP). Progress in neonatal resuscitation in developing countries has led to the survival of an increasing number of premature infants, resulting in an increased rate of ROP and consequently in visual disability. Strategies to reduce ROP involve optimizing oxygen saturation, nutrition, and normalizing factors such as insulin-like growth factor 1 and n-3 long-chain polyunsaturated fatty acids (LC-PUFA). Our previous study, OmegaROP, showed that there is an accumulation or retention of docosahexaenoic acid (DHA) in mothers of infants developing ROP, suggesting abnormalities in the LC-PUFA placental transfer via fatty acid transporting proteins. The present study aims to better understand the LC-PUFA transport dysfunction in the fetoplacental unit during pregnancy and to find a novel target for the prevention of ROP development.

**Methods:**

The study protocol is designed to evaluate the correlation between the expression level of placental fatty acid receptors and ROP occurrence. This ongoing study will include 100 mother-infant dyads: mother-infant dyads born before 29 weeks of gestational age (GA) and mother-infant dyads with full-term pregnancies. Recruitment is planned over a period of 46 months. Maternal and cord blood samples as well as placental tissue samples will be taken following delivery. ROP screening will be performed using wide-field camera imaging according to the International Classification of ROP consensus statement.

**Discussion:**

The results of this study will have a tangible impact on public health. Indeed, if we show a correlation between the expression level of placental omega-3 receptors and the occurrence of ROP, it would be an essential step in discovering novel pathophysiological mechanisms involved in this retinopathy.

**Trial registration:**

NCT04819893.

## Background

Physiologically, the retina does not have blood vessels until the fourth month of gestation, and the temporal periphery is normally fully vascularized by 1 month after birth. Incomplete vascularization of the retina in preterm infants carries a risk of retinopathy of prematurity (ROP) [1]. Therefore, screening for ROP is recommended in infants born before 30 weeks of gestational age (GA) or those weighing less than 1500 g [2]. ROP is a pathological process in the immature retina leading to retinal neovascularization complications such as tractional retinal detachment, which results in subsequent visual loss. The incidence of ROP in developed countries is highly variable and ranges from 6 to 34% [3]. Despite improvements in controlling risk factors, ROP remains a leading cause of blindness. Although progress in neonatal resuscitation has led to the survival of an increasing number of premature infants, especially in developing countries, the rates of ROP and resulting visual loss have risen simultaneously [3–5]. High oxygenation targets are associated with decreased mortality, but hyperoxia inhibits the development of retinal vascularization. Subsequently, the increased retinal metabolic activity triggers growth factor-induced retinal vasoproliferation in the poorly vascularized retina [6]. Depending on the location and stage of the ROP, intravitreal vascular endothelial growth factor (VEGF) inhibitor or laser ablation of non-vascularized retinal areas reduces the risk of blindness related to ROP have shown satisfactory outcomes, still some treated infants do not achieve good long-term visual acuity due to several other complications related to the disease. Therefore, prevention through the control of risk factors is more effective than late treatment of neovascularization. Strategies to reduce ROP involve optimizing oxygen saturation, nutrition, and normalizing factors such as insulin-like growth factor 1 (IGF-1) and omega 3 (n-3) long-chain polyunsaturated fatty acids fatty acids (LC-PUFA) [7].

The mechanisms of normal and pathological retinal vascular development have already been extensively studied in ROP. Among the factors influencing the abnormal vascularization process in ROP are PUFAs and/or their derivatives, which appear to be potent retinal vascular growth regulators. For example, n-3 PUFAs have been shown to prevent pathological angiogenesis in age-related macular degeneration [8–12], retinal vascular damage in diabetes [13], and abnormal retinal vascular development in an animal model of ROP (model of oxygen-induced retinopathy) [14].

Docosahexaenoic acid (DHA) is protective in experimental models, but its administration as part of parenteral nutrition has yielded inconsistent results. According to the literature, few studies have been performed in vivo with extremely preterm infants. Some studies have not found a correlation between ROP development and DHA supplementation [15, 16], whereas others have [17–19]. According to Berbade-Garcia and colleagues, it seems that LC-PUFA supplementation is correlated with a lower occurrence of severe ROP [20].

Concerning molecular signaling pathways, PUFAs modulate IGF-1 activation pathways [21] and VEGF-induced endothelial cell proliferation [22, 23]. These signaling pathways are implicated in the pathophysiology of ROP [24–26]. Postmortem studies have shown that the fatty acid composition of erythrocytes is correlated with that of nerve structures in children [27]. The pre- and postnatal developmental period is the most active phase of LC-PUFA incorporation into the central nervous system, including the retina [28].

Since retinal lipid analysis in humans is inconceivable due to its invasive nature, biochemists use circulating biomarkers of retinal LC-PUFAs. The lipid composition of erythrocyte membranes is considered a more reliable reflection than plasma since lipids in red blood cells are less sensitive to external factors. The omega-3 LC-PUFA composition of erythrocyte membranes does not appear to vary significantly in healthy children during the last weeks of gestation (4.7 ± 1.3% of total fatty acids for DHA at 24 GA [29], 5.2 ± 0.7% at 29 GA [30], 4.6 ± 0.4% at 33 GA [31], and 4.1% with a CI = [1.71–4.86] at 29 GA [32]). DHA is essential for fetal development and cannot be synthesized by the fetus. During pregnancy, fatty acids (FAs) are transferred from the maternal blood to the fetal blood via the placenta and the umbilical cord. At the microvillous membrane of the placenta, lipoprotein lipase induces the catabolism of triglycerides from the maternal blood, followed by placental uptake of free FA products. LC-PUFAs cross the microvillous membrane, the syncytium, and the basement membrane to reach the fetal blood circulation. The transport of nutrients and solutes across the syncytiotrophoblast occurs through several passive and active processes, including flow-limited diffusion, transcellular diffusion, protein-mediated transfer, and endocytosis/exocytosis. Selective transport of long-chain fatty acids occurs via specific transporters called fatty acid-binding protein (FABP) and fatty acid-transporting protein (FATP). These proteins have a major role in the transport of Fas [33, 34]. FATP1 and FATP4 are frequently studied in placental tissue since their expression is correlated with DHA levels in maternal plasma, cord blood, and placental phospholipids, suggesting an essential role in the transfer of LC-PUFA [35]. Recent research is beginning to uncover the mechanisms of DHA transmembrane and intracellular transport in the placenta. It is suggested that maternal health and nutrition during pregnancy could be important in determining FA transport and binding protein expression and, thereby, essential FA delivery to the fetus. Further knowledge in this domain may be the first step in developing targeted interventions to help optimize fetal retinal growth and limit the incidence of ROP.

Our previous study, Omega-ROP, took place at Dijon University Hospital’s ophthalmology and neonatology departments and the National Research Institute for Agriculture, Food and the Environment (INRAE) between July 2015 and January 2018. This project confirmed previously published reports that the bioavailability of circulating (erythrocyte) LC-PUFAs was different in premature newborns developing ROP than in those without ROP [32]. Interestingly, it also showed that blood omega-3 LC-PUFA levels in mothers of premature newborns varied in opposite directions to their newborns. Mothers of newborns developing ROP had increased erythrocyte DHA levels above the normal range found in middle-aged women [36], while the levels of their respective newborns were abnormally low. Thus, our data suggest a potential accumulation or retention of DHA in mothers of infants developing ROP due to a dysfunction in LC-PUFA trans-placental transfer [32]. We decided to continue and extend our research collaboration based on these findings. Therefore, an amendment to collaborate with Necker Hospital in Paris was made for the study to be a multicenter trial.

The present study aims to better understand the underlying cellular and molecular mechanisms by assessing the association between placental FA receptor expression levels and the incidence of ROP in newborns. In addition, we will study the association between the LC-PUFA content of cord blood and maternal blood with the expression level of placental PUFA receptors and their correlation with ROP severity.

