### Assessment of variables

#### Maternal history collection

Maternal history that may cause changes in placental function will be recorded, for example, pregnancy-induced hypertension, pre-eclampsia, abruptio placentae, and autoimmune and thromboembolic diseases during the pregnancy (Table 2). The investigator will give this document to the patient following delivery.

**Table 2 Tab2:** Maternal characteristics

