**Inclusion number**	
**Age**	
**Pre-pregnancy weight (kg)**	
**End of pregnancy weight (kg)**	
**Size (cm)**	
**Smoking (during pregnancy)**	
**Alcohol (during pregnancy)**	
**Taking medication**	
**Multiple pregnancies?**	
**Delivery route**	
**Primipara?**	
**Diabetes (before pregnancy), if yes, HbA1c (%)**	

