**Dyslipidemia**	
**Arterial hypertension**	
**Digestive diseases (please specify)**	
**Thromboembolic diseases**	
**Dysimmune diseases**	
**Obstetrical history (please specify)**	
Events during this pregnancy	

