## Statistical methods

The data will be reviewed at the end of the study before statistical analysis. Statistical analysis will be performed using STATA v15.1 (StataCorp, College Station, TX, USA).

Quantitative data will be expressed as median and interquartile range [IQR]. The groups will be compared for quantitative variables using parametric or non-parametric tests according to normal/abnormal data distribution, and for qualitative variables using the chi-square test or Fisher’s exact test. Spearman correlations will be used to analyze the extent to which the placental FA receptor expression is associated with ROP occurrence. The extent to which the placental FA receptor expression is associated with the maternal blood FA level and the blood cord FA level will be analyzed through Spearman correlations. Linear regression analyses will be carried out to compare placental FA receptor expression levels as a function of GA. Statistical significance is to be set at *p* < 0.05, and the tests will be two-tailed.

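### Secondary outcomes 1 and 2 rest on unadjusted Spearman correlations, so a recorded maternal factor that also affects blood fatty acids outside the receptor could contribute to the result; an adjusted coefficient should be reported beside each one

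*Protocol article*

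**What the plan says.** Secondary outcomes 1 and 2 (Protocol article, Outcomes) relate cord blood and maternal blood fatty acid (FA) content, respectively, to placental FA receptor expression. The Statistical methods section fixes how: the extent to which receptor expression "is associated with the maternal blood FA level and the blood cord FA level will be analyzed through Spearman correlations". It names no covariate, stratum or partial correlation for them.

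The only regression in that section is a different analysis, with no FA term: "Linear regression analyses will be carried out to compare placental FA receptor expression levels as a function of GA". Multiple regression is mentioned only under Sample size calculation, for a difference between groups.

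On maternal factors, the Background suggests that "maternal health and nutrition during pregnancy could be important in determining FA transport and binding protein expression", and the same sentence goes on to make FA delivery to the fetus a consequence of that expression. The section Maternal history collection gives the reason for the data form: "Maternal history that may cause changes in placental function will be recorded". Table 2 includes pre-pregnancy weight, height, "Diabetes (before pregnancy), if yes, HbA1c" and "Dyslipidemia".

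Table 1 excludes obstetrical pathology, including gestational diabetes, in full-term mothers only. It lists pre-pregnancy diabetes, dyslipidemia and high body weight as exclusions in neither group.

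**The concern.** The study collects maternal factors because they may change the placenta, then leaves them out of the only analyses that link receptor expression to blood FA. A factor that moves expression and also moves blood FA by a separate route would produce a correlation between the two even if the receptor had no effect on FA status. Restriction does not prevent this, because the pre-pregnancy factors are admitted in both groups. Analysing preterm and full-term dyads separately would not remove it either.

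At stake is how the two results are read. The abstract aims to understand a transport dysfunction in the fetoplacental unit and to find a target for prevention. A correlation that arose partly from maternal adiposity or a lipid disorder could be taken as support for that mechanism. The point is confined to secondary outcomes 1 and 2 and does not concern the analysis of receptors against ROP.

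**Working it through.** The plan gives no expected correlation for these outcomes, so there is no figure of its own to reproduce. The check asks how far a shared cause alone could move the planned test.

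**Inputs from the document.** n = 70 (preterm dyads) or 100 (all dyads), from Sample size calculation; two-sided 0.05, from Statistical methods.

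**Assumptions.** One maternal factor M is continuous and measured without error. It has the same correlation l with receptor expression and with a blood FA. There is no direct link between expression and FA. The document gives no value for l, so a range is shown.

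**Step 1, induced correlation.** The Pearson correlation between FA and expression is l × l. For normal variables Spearman's coefficient is (6/π) × arcsin(l²/2). For l = 0.2, 0.3, 0.4 and 0.5, l² = 0.04, 0.09, 0.16 and 0.25, and Spearman's coefficient is about 0.04, 0.09, 0.15 and 0.24.

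**Step 2, chance of p < 0.05** (simulation, 20,000 replicates per setting):

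| l | Unadjusted, n = 70 | Unadjusted, n = 100 | Partial Spearman given M |
|---|---|---|---|
| 0.2 | 5.9% | 7.0% | 5-6% |
| 0.3 | 10.8% | 13.8% | 5-6% |
| 0.4 | 23.7% | 32.5% | 5-6% |
| 0.5 | 51.0% | 66.6% | 5-6% |

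An independent run of 3,000 replicates for l = 0.3, 0.4 and 0.5 gave 12%, 23% and 52% at n = 70, and 13%, 31% and 66% at n = 100. A normal approximation agrees. At l = 0.3 and n = 70, z = atanh(0.086) × √67 / 1.03 ≈ 0.68, which gives about 10.5%.

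**Step 3, are the upper values realistic?** For a yes/no factor with prevalence p, a correlation r requires a mean shift of r / √[(1 − r²) p (1 − p)] within-group SDs, here in both variables.
- p = 5% (assumed): r = 0.3 needs 0.3 / √(0.91 × 0.0475) ≈ 1.4 SD; r = 0.5 needs 0.5 / √(0.75 × 0.0475) ≈ 2.6 SD.
- p = 10% (assumed): about 1.0 and 1.9 SD.

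Shifts of that size in both variables are unlikely for uncommon diagnoses. The upper rows are more relevant to a continuous factor such as BMI, and the document does not support those values for BMI either.

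**Step 4, cost of adjusting when it is not needed.** Suppose M acts on FA only through the receptor, with an assumed receptor-FA correlation of 0.4 and n = 70. Power is about 91% unadjusted. After adjusting for an M correlated 0.3 to 0.5 with expression, it is about 89% down to 82%.

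**The case against.** The strongest reply is that the document does not establish a confounder. The Background sentence runs from maternal health to transporter expression and from there to fetal FA. That is a chain through the receptor, and on it the unadjusted cord correlation reflects real transport. A common cause also needs a route from maternal status to FA that avoids the receptor, and no section states one. The measured quantity is a percentage composition of erythrocyte lipids, and the Background prefers erythrocytes because they are less sensitive to outside influences than plasma. All of this stands. A reader might infer that the protocol itself names metabolic status as a cause of both variables; it does not.

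Other parts also stand. Every path strength in the calculation is assumed. Diet, the other half of what the Background names, is not in Table 2 and cannot be adjusted for. Adjusting for metabolic factors alone would leave preterm and full-term dyads mixed in a pooled correlation. Both outcomes are framed as relationships, and the Discussion says mechanistic studies are needed, so it would go too far to say the protocol offers these correlations as proof that receptors govern FA status.

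Two parts do not stand. Adjustment would not remove most of the genuine signal: on the purely mediated path the loss of power is small (Step 4). Nor is this merely detail left to an analysis plan that is not shown. The article states a method for these two outcomes, and that method is unadjusted. An analysis plan could add to it, but the stated choice can be judged as it is.

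**Conclusion.** The point holds in a conditional form. The stated analyses for secondary outcomes 1 and 2 use none of the maternal factors that the protocol records as possible influences on the placenta. If one of those factors also affects blood FA outside the receptor, part of the correlation is not transport. Whether that happens, and how strongly, cannot be learned from the document.

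Under the assumed range, the false-positive rate at 70 dyads runs from close to nominal (6-7% at a correlation of 0.2) through 11% and 24% to 51% (at 0.5). A reader might conclude that half of such findings would be spurious. The document does not support that: 51% is the top of an assumed grid, for one perfectly measured continuous factor. Likewise, the return to about 5% after adjustment holds only if the true cause is fully captured. The case for change is that the remedy uses data already collected and costs little.

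**What to change.** For secondary outcomes 1 and 2, keep the unadjusted Spearman coefficient and report beside it a pre-specified partial Spearman correlation (or rank regression), adjusted for:
- gestational age or preterm/term group;
- pre-pregnancy BMI, from the weight and height in Table 2;
- one yes/no term for pre-pregnancy diabetes or dyslipidemia.

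Gestational age or group belongs in the set because the plan already models expression as a function of it, and because the Discussion cites maternal erythrocyte DHA of 5.5 to 5.8% at full term against 2.5% in mothers of 33-week preterm infants.

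Base any transport interpretation on the adjusted result, and state that diet is not recorded, so residual confounding by nutrition remains.

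The cost is analysis wording only, with no new data. Three covariates reduce the residual degrees of freedom from 68 to 65 with 70 dyads, or from 98 to 95 with 100. There is a small loss of power if adjustment proves unnecessary, and dyads with missing weight or height drop out of the adjusted analysis.

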## Methods

### Study design

Initially, the OMEGAROP-2 clinical trial (NCT04819893) was a single-center prospective cohort study. However, ROP is an uncommon pathology, with an incidence of approximately 20% in preterm newborns under 29 GA. Therefore, our protocol was amended to extend recruitment from 22 to 46 months at the Dijon University Hospital Maternity Department and to make the study a multicenter project with the collaboration of the ophthalmology and gynecology departments of Necker Hospital, Paris, France, to increase the number of participants.

### Study population and schedule

The design of the study is illustrated in Fig. 1.

**Fig. 1 Fig1:**
[figure not shown]
Flowchart of the OmegaROP-2 study

For mother-infant dyads born before 29 GA, screening will be performed in the Pathological Pregnancy Department. Screening will be carried out in the delivery room for patients delivering at full-term. First, the investigating physician provides the patient with information and answers questions about the research study’s purpose and requirements. They also specify the patient’s rights when participating in biomedical research and verify the eligibility criteria. Second, the investigator obtains the patient’s freely given, informed, and written consent. Finally, the investigator provides a copy of the informed consent form according to article L1122-1 of the Public Health Code. Patients who do not consent to the trial will be treated according to standard care. The “prematurity ROP group” will be defined as patients with infants developing ROP type 1 or 2 (visible on fundus examination after 4 weeks of life and at least 31 GA) and born before 29 GA. The “prematurity no-ROP group” will be defined as patients with infants without any stage of ROP and born before 29 GA. The “full-term no ROP group” will comprise patients with infants without ROP and born at full-term. Mother-infant dyads in life-threatening conditions will not be included (Table 1).

**Table 1 Tab1:** Inclusion and exclusion criteria

Inclusion criteria	Exclusion criteria
Mothers delivering a premature newborn of less than 29 weeks’ gestational age (GA) after obtaining their non-opposition	Mothers giving birth between 29 and 38 GA + 6 days
Mothers giving birth at full term between 39 and 41 GA + 6 days, after obtaining their non-opposition	Mothers with a vital prognosis
The mother must be of legal age	The mother is not affiliated with a social security system
The mother must not be under legal guardianship	For full-term mothers: Current or previous history of an obstetrical pathology of any origin (vascular such as gestational hypertension, pre-eclampsia; gestational diabetes; intrauterine growth retardation, maternal infection during pregnancy such as toxoplasmosis, cytomegalovirus, rubella, measles, chickenpox)

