If necessary, transpupillary laser treatment of the ischemic areas will be performed under general anesthesia. This treatment will be carried out at the Fondation Ophtalmologique Adolphe de Rothschild, Paris, France; the treatment involves " + " attacks in zone I, stage 3 in zone I, and stages 2 and 3 " + " in zone II [38]. Significant risk factors for developing ROP, namely, term and weight at birth, duration of mechanical ventilation, sepsis, use of erythropoietin, red blood cell transfusion, and cerebral hemorrhage will be documented during the first month of life (Table 4).

**Table 4 Tab4:** Newborn characteristics

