**Inclusion number**	
Date of birth	
Term of birth (GA)	
Birth weight (g)	
Fetal growth restriction	< 10th percentile? < 5th percentile? Causes: Maternal? Fetal? Placental?
Weight to W1/W2/W3/W4 (g)	
Gender	Male / Female
Oxygen therapy:	Total duration (days): Duration of mechanical ventilation (days): Duration of CPAP (days): Duration of HFNC (days): Duration of simple nasal cannula (days): Maximum FiO_2_ (%):
Sepsis	Yes/No
Necrotizing enterocolitis	Stage I / II / III? Required surgical management? Yes/No
Neurologic conditions	Intracranial hemorrhage (specify the grade): Periventricular hemorrhage (specify the grade): Subependymal hemorrhage (specify the grade): Periventricular leukomalacia (specify the grade):
Anemia	Minimum hemoglobin level: Transfusion (specify the number of units and quantity): EPO use?
Ophthalmologic follow-up	Date of first fundus: Week of life at first fundus: Week of gestation at first fundus: Date of fundus at first sign of ROP: Week of life at first sign of ROP: Week of gestation at first sign of ROP: Stage of ROP at first sign of ROP: Localization of ROP at first sign of ROP: Stage plus or pre-plus: ROP type 1 or 2: Most severe eye: Date of fundus at maximal ROP: Week of life at maximal ROP: Week of gestation at maximal ROP: Number of fundus before first sign of ROP: Number of fundus before maximal ROP: Total number of fundus with RETCAM: Laser treatment (which eye?): Date of laser treatment: Intravitreal treatment (bevacizumab) (which eye?): Date of intravitreal treatment:
Date of discharge (specify if transferred to another hospital)	

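### The receptor–ROP correlation is unadjusted for recorded hypertensive disease of pregnancy, and the full-term group is a disease-free comparator that should be kept out of it

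*Protocol article*

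**What the plan says.** Eligibility is in Table 1 of the Protocol article (Study population and schedule). The preterm criterion is "Mothers delivering a premature newborn of less than 29 weeks’ gestational age (GA) after obtaining their non-opposition", and recruitment takes place where one expects complicated pregnancies: "For mother-infant dyads born before 29 GA, screening will be performed in the Pathological Pregnancy Department". The obstetric exclusion reads "For full-term mothers: Current or previous history of an obstetrical pathology of any origin". Its examples are gestational hypertension, pre-eclampsia, gestational diabetes, growth retardation and several infections. One medical restriction covers every group: "Mother-infant dyads in life-threatening conditions will not be included".

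Under Maternal history collection, the article gives its reason for recording disease: "Maternal history that may cause changes in placental function will be recorded, for example, pregnancy-induced hypertension, pre-eclampsia, abruptio placentae". Table 2 has rows for gestational hypertension, pre-eclampsia and eclampsia. Under Newborn follow-up it lists "Significant risk factors for developing ROP, namely, term and weight at birth", among other factors. Table 4 has a row for "Fetal growth restriction", with percentile cut-offs and a maternal, fetal or placental cause.

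The primary outcome is the relationship between placental receptor expression and ROP occurrence. Statistical methods assigns it a Spearman correlation. The only regression named there relates expression to gestational age. The text does not say whether the correlation uses the 70 preterm dyads or all 100.

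**The concern.** Placental receptor expression is the exposure. The protocol itself says that hypertensive disease may alter the organ in which it is measured. If that disease is also more or less frequent among infants who develop ROP, expression and ROP will be correlated with no transport mechanism behind it. Gestational age does not remove this, because two infants born in the same week can come from a pre-eclamptic and a normotensive pregnancy. A Spearman correlation as stated has no place for the recorded disease.

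The full-term group raises a different problem. Those mothers are selected to be free of obstetrical disease, and their infants are all no-ROP by design, since the article says ROP does not occur at term. If they are pooled into the no-ROP side, 30 healthy placentas join one side only.

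At stake is the intended reading of a positive result, which the abstract presents as a step towards a new disease mechanism.

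**Working it through.** **Inputs from the article.** 70 preterm and 30 full-term dyads (Sample size calculation); ROP incidence of about 20% before 29 weeks (Study design), so 0.20 × 70 = 14 ROP and 56 no-ROP; two-sided 5% level (Statistical methods).

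**Assumed inputs.** The article gives no disease prevalence, no shift in expression with disease and no link between disease and ROP. All three are varied below.

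**Point 1, within the preterm dyads.** Let a proportion p1 of ROP dyads and p0 of no-ROP dyads have the disease, and let disease shift mean expression by s (in SDs among dyads of the same disease status). With no true receptor–ROP link, the expected spurious difference is s × (p1 − p0). False-positive rates come from simulation with 6,000 runs per row. Near 11% the Monte Carlo standard error is √(0.11 × 0.89 / 6000) ≈ 0.4 percentage points.

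| p1 vs p0 | s | Spurious difference | Unadjusted Spearman |
|---|---|---|---|
| 60% vs 25% | 1.0 | 1.0 × 0.35 = 0.35 SD | 17–18% |
| 50% vs 25% | 1.0 | 1.0 × 0.25 = 0.25 SD | 11–12% |
| 50% vs 25% | 0.5 | 0.5 × 0.25 = 0.125 SD | about 7% |
| 40% vs 30% | 1.0 | 1.0 × 0.10 = 0.10 SD | about 6% |
| 35% vs 25% | 0.5 | 0.5 × 0.10 = 0.05 SD | about 5% |

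A linear model of expression on ROP and disease gives 4 to 5% in the first four rows.

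**Point 2, contrasts that use the full-term dyads.** A second null simulation (2,000 runs per cell) kept overall ROP at 20% of 70. It set disease prevalence among preterm dyads, the shift, and the risk ratio of ROP with disease, and added 30 disease-free full-term dyads.

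- 40% prevalence, 1 SD shift, risk ratio 3: 28% false positives with all 100 pooled, 16% for preterm-only Spearman, 5% for preterm adjusted.
- Risk ratio 1 (disease unrelated to ROP), shift 0.5 or 1 SD: preterm-only Spearman stays at 4 to 6%, while pooling gives 5 to 10%.
- Preterm versus full-term t-test when prematurity itself has no effect on expression, shift 0.5 or 1 SD: rejection in 6 to 13% of runs at 20% prevalence and 26 to 73% at 60%.

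The risk-ratio-1 result separates the two mechanisms. Within the preterm dyads, nothing is inflated unless disease is linked to both expression and ROP. The one-sided exclusion acts only when full-term dyads enter the contrast.

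**The case against.** A reader might infer that Table 1's one-sided exclusion by itself creates a false receptor effect on ROP. The documents do not support that. Both preterm groups enter under the same criteria, so Table 1 creates no imbalance between them. The within-preterm risk comes from the unadjusted test.

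Four further objections have weight.

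- **No single condition is tied to both sides.** The article links hypertension and pre-eclampsia to placental function, and birth weight to ROP. It does not say that hypertensive disease affects ROP. The confounding is therefore conditional, and the milder scenarios stay close to 5%.
- **The recorded data are not wholly unused.** Statistical methods provides for group comparisons of quantitative and qualitative variables, which would presumably show an imbalance in pre-eclampsia. Seeing an imbalance does not correct the correlation.
- **This is a condensed article.** An analysis plan that is not shown may specify adjustment, and the sample size paragraph mentions multiple regression without naming covariates. The point stands because the article does fix a method for the primary question, and that method takes no covariate.
- **Adjusting for growth restriction could do harm.** The Discussion describes fatty acids as essential for fetal growth and as crossing by specific transporters. Growth restriction may therefore result from the exposure, and conditioning on it could remove part of the effect sought. This stands and shapes the fix.

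It would also be too strong to say that preterm mothers enter without any medical restriction, since life-threatening conditions are excluded. Nor does the article list a preterm versus full-term contrast as an outcome or claim to isolate prematurity. A healthy term reference group is a legitimate choice if it is labelled as one.

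**Conclusion.** The point holds in two limited parts. (1) The stated primary analysis leaves out a recorded condition that the protocol itself regards as able to change the placenta. If that condition differs between preterm ROP and no-ROP dyads, false positives run from 6–7% to 11–18% over the scenarios with a shift of 1 SD, or of 0.5 SD with a two-fold imbalance. At 35% versus 25% with a 0.5 SD shift there is almost no inflation. Every figure rests on assumed prevalences and shifts. (2) Contrasts with the full-term dyads compare preterm birth of any cause with uncomplicated term pregnancy. Pooling those dyads into the primary correlation would add to the distortion, and the text does not rule pooling out. Neither part calls the eligibility rule wrong. The change is worth making because it costs little and recruitment was still open when the article was written.

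**What to change.** 1. State that the primary comparison is ROP versus no-ROP **within the preterm dyads**. Use a partial rank correlation, or a linear model of expression on ROP, with gestational age and one yes/no covariate for recorded hypertensive disease of pregnancy (gestational hypertension, pre-eclampsia or eclampsia).
2. Add growth restriction below the 10th percentile only in a sensitivity analysis, and say that it may lie on the causal path.
3. Keep Table 1 as it is. Do not place the full-term dyads on the no-ROP side of the primary correlation.
4. Label any contrast with them as preterm birth of any cause versus uncomplicated term pregnancy. Add a sensitivity analysis restricted to preterm dyads that have none of the obstetric conditions listed in Table 1. Use the listed conditions, because preterm delivery could itself be read as an obstetrical pathology.

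**Cost.** All variables are already in Tables 2 and 4. The disease covariate takes one degree of freedom: with an intercept, ROP, gestational age and disease, 70 − 4 = 66 remain. With about 14 ROP cases, a long covariate list should be avoided. The restricted analysis has a wider interval. If 20% to 60% of preterm dyads were removed (assumed), 56 to 28 would remain. At equal SD, the standard error factor √(1/n + 1/30) rises from 0.218 at n = 70 to 0.226 at n = 56 or 0.263 at n = 28, about 4% to 20% wider.
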